##### Sociodemographic data

2.4.9.6

Background characteristics of study participants, including the demographic and socioeconomic status, family members, reproductive and morbidity history of the mother, will be collected using a structured questionnaire (adapted from the National Family and Health Survey-5 household tool). The age of the child will be calculated based on the date of birth recorded from the birth certificate/record/discharge record. In the absence of any official birth records, the date of birth as reported by the mother/primary caretaker will be used. The socioeconomic status of the households will be captured using the Kuppuswamy scale.

In addition, a random sample of THR products will be analyzed for nutrient composition and bacterial content in NABL-accredited labs.

The participant timelines of data collection and analyses for different components are summarized in Table 3.

**Table 3 tab3:** Participant timelines (53) outlining enrollment, interventions, and scheduled assessments in Phase 3.

Activities and data components	Time points					
	Enrollment	Month 0 (baseline assessment)	Month 6	Month 12	Month 18	Month 24 (endline assessment)
Enrollment						
Eligibility screen	X					
Informed consent	X					
Randomization	X					
Intervention/comparator						
Improved THR and SBCC						
Existing THR and SBCC						
Data collection						
I. Longitudinal component						
Socio-demographic information		X				X
Anthropometry indicators (weight, length/height, MUAC)		X	X	X	X	X
IYCF and nutritional practices, household food security		X	X	X	X	X
WASH practices		X	X	X	X	X
Health status		X	X	X	X	X
THR utilization		X	X	X	X	X
II. Cross-sectional component						
Anthropometry indicators (weight, length/height, MUAC)		X	X	X	X	X
THR utilization		X	X	X	X	X
Generic data						
Nutrient composition of improved THR		X				
Data collection for economic evaluation and analysis		X	X	X	X	X

Data collection team (OAT members) will receive rigorous training in anthropometric measurements according to standard protocols, as well as in the administration of study tools and data capture procedures. Additionally, intrarater and interrater reliability testing for anthropometry measurements will be undertaken across sites and data collectors. The data collected will be reviewed periodically to ensure accuracy and reduce missing outcome data.

#### Data management

2.4.10

Data will be collected electronically using the REDCap application, an Electronic Data Capture (EDC) tool with built-in logic and consistency checks. To protect the confidentiality of participants, data collection and storage procedures will be regulatory compliant, restricting access to data on devices through passwords.

The data collectors will work in pairs in the field to administer questionnaires and measure children’s anthropometry. A field supervisor will be responsible for planning the data collection and coordinating data collection activities at each study site. As a routine quality control measure to maintain data integrity, repeat data collection will be conducted by field supervisors in a randomly selected 5% of the participants sampled across the clusters. The supervisor will report directly to the data management team. Data will be uploaded to the designated server daily by data collectors and checked weekly by the data management team. The errors or incomplete questionnaires identified will be sent back to the data collection teams to complete the questionnaire with participants. Data collectors will attempt to reach participants at least three times before participants are considered to be lost to follow-up for that data collection point. Monthly project management meetings will be held to track data quality throughout the trial. Only the data management team and investigators will have access to the complete dataset.

#### Statistical analysis plan

2.4.11

Baseline characteristics of study participants, along with primary and secondary outcome variables, will be summarized by study groups using appropriate descriptive statistics depending on the measurement scale and data distribution. Continuous variables will be reported as means with standard deviations or medians with interquartile ranges, as appropriate, while categorical variables will be presented as frequencies and percentages, with 95% confidence intervals provided where applicable.

Dietary data captured through 24-h dietary recall will be utilized for calculating the ‘usual intake’, diet diversity, minimum meal frequency and minimum adequate diet. Using DietCal software (version 15.1.1), the reported amounts of raw foods in 24-h dietary recall will be entered, and converted to intake of different food groups, and macro- and micronutrients. The macronutrient and micronutrient intakes will then be transformed using a linear mixed-effect regression model. The values predicted using the linear mixed-effect regression model will be back-transformed to compute the “usual nutrient intake” (54). The estimated average requirement (EAR) cut-point method and full probability approach (for iron) will be used to estimate the prevalence of nutrient inadequacy of complementary feeding using the WHO recommendation outlined in Dewey et.al 2002 for children 6 months to 24 months and national recommendations for children above 24 months of age (55, 56). The raw dietary intake data will also be used to assess the dietary diversity, minimum meal frequency and minimum acceptable diet in these children (55).

The individual longitudinal assessment of WHO standardized anthropometric scores will be compared between the intervention and comparator groups using an intention-to-treat analysis (57). A linear mixed effects model with subject and cluster as random effects and an interaction term for time and intervention group will be performed. Separate analysis will be performed for WAZ, LAZ and WHZ. The stunting, wasting, and underweight prevalence among all THR beneficiaries in the recruited AWCs at the end of the intervention period will be compared between the intervention and comparator groups using log binomial regression, robust estimates of standard error accounting for clustering. Potential confounders (household food security, education, socioeconomic status, etc.) will be considered in the model. All episodes of illness or sickness occurring during the period of participation will be systematically recorded in the study data. For outcome assessment, illnesses with the potential to influence child growth trajectories will be accounted for during analysis through appropriate statistical adjustments and sensitivity analyses, as applicable.

All analyses will be performed within each site and across all sites by pooling the data. Analyses will be conducted using Stata statistical software (StataCorp LLC, College Station, Texas, United States), with two-sided tests and a significance threshold of *p* < 0.05.

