###### Secondary outcomes

2.4.5.2

For children aged 6–36 months enrolled in the longitudinal component: nutritional status based on WAZ, HAZ, WHZ, and MUAC, IYCF practices, dietary and nutritional intake, water, sanitation and hygiene (WASH) practices, and health status.For children aged 6–36 months assessed under the cross-sectional component: nutritional status based on WAZ, HAZ, and WHZ, and acceptance and usage of THR.Other outcome indicators- Cost-effectiveness of the intervention: The incremental cost-effectiveness of implementing the intervention package will be compared with the existing THR and SBCC strategy in the study district.

Details of the outcome indicators to be assessed in Phase 3 are presented in Supplementary Table 3.

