##### Infant and young child feeding practices

2.4.9.2

Data on IYCF practices, including breastfeeding and complementary feeding, will be collected using a structured IYCF questionnaire, along with a 24-h dietary recall survey. WHO recommended core indicators of optimal breastfeeding, including exclusive breastfeeding till 6 months, continued breastfeeding for at least two years post-birth, along with complementary feeding practices, such as introduction of solid, semi-solid, or soft foods, minimum dietary diversity, minimum meal frequency, minimum acceptable diet, consumption of iron-rich or iron-fortified foods from postnatal 6 completed months and nutrient intake will be captured (49). Apart from a pre-tested questionnaire on IYCF practices, a two non-consecutive 24-h dietary recall survey will be administered on the mother/primary caregiver for assessing the dietary and nutrient intake of children enrolled for the longitudinal study. Respondents will include mothers and/or primary caregivers within the household. During this dietary survey, respondents will be asked to recall a detailed food intake of the child during the past 24 h. A standard food recall kit (measuring cups, spoons and food picture flip book) will be used by the interviewer for portion size estimation.

Household food security information will be collected using a questionnaire adapted from the food security and nutrition surveillance tool (50, 51).

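### Defining usual nutrient intake as back-transformed mixed-model predictions gives a distribution that is too narrow and possibly shifted, so EAR-based prevalence of inadequacy is biased in a direction the article does not fix

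*Protocol article*

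**What the plan says.** Section 2.4.9.2 (Infant and young child feeding practices) plans that "a two non-consecutive 24-h dietary recall survey will be administered on the mother/primary caregiver"; this applies to the cohort children. Table 3, under section 2.4.9.6 (Sociodemographic data), marks the row "IYCF and nutritional practices, household food security" at months 0, 6, 12, 18 and 24.

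Section 2.4.11 (Statistical analysis plan) gives the processing in three steps:

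1. Modelling: "The macronutrient and micronutrient intakes will then be transformed using a linear mixed-effect regression model".
2. Definition of usual intake, with a literature citation: "The values predicted using the linear mixed-effect regression model will be back-transformed to compute the “usual nutrient intake".
3. Use of the result: "The estimated average requirement (EAR) cut-point method and full probability approach (for iron) will be used to estimate the prevalence of nutrient inadequacy".

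The section mentions no rescaling of predictions, simulation from variance components or correction on back-transformation. It does not name the transformation or the model terms, or say whether rounds are modelled separately or together. Section 2.4.5.2 (Secondary outcomes) lists, for the cohort, "IYCF practices, dietary and nutritional intake, water, sanitation and hygiene (WASH) practices, and health status".

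**The concern.** The EAR cut-point method estimates a tail area: the share of children whose usual intake lies below the requirement. It therefore needs the spread of usual intake to be right, as well as its centre.

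A mixed-model prediction for a child is a compromise between that child's few recalls and the overall mean. It is a sensible estimate for one child, but a set of such predictions varies less than the true usual intakes do. Counting how many fall below a cut-point gives the wrong share unless the cut-point sits at the median. Predictions from the fixed part alone would carry no residual child-level variation and be narrower still.

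There is a second, separate problem. If the model is fitted on a log-type scale and the prediction is simply back-transformed, the result is the median of a child's daily intake. Usual intake is the mean over days, which is higher for skewed nutrients.

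At stake are the reported inadequacy prevalences, which speak directly to whether complementary diets meet requirements.

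**Working it through.** **No figure to reproduce.** The article states no number for this step. The check shows what the stated procedure returns when the truth is known.

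**Inputs**
- Recalls per child per round: k = 2 (section 2.4.9.2).
- Rounds: 5 (Table 3). If all were modelled jointly as one stable intake, k = 10. The article does not say this is done.
- Within/between-child variance ratio r: not given; assumed 1, 2 and 4.
- Transformation: not given. Log is assumed for the second part, with between-child log SD σ_b = 0.4, so within-child variance σ_w² = 0.16r.
- EAR position d, in between-child SDs from the mean on the transformed scale: assumed −1 and +0.5.
- Model: intercept plus child effect.

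**Step 1: spread of the predictions.** Variance of predictions = λσ_b², with λ = 1/(1 + r/k). The SD ratio is √λ.

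| r | k = 2: λ | k = 2: SD ratio | k = 10: SD ratio |
|---|---|---|---|
| 1 | 0.667 | 0.82 | 0.95 |
| 2 | 0.500 | 0.71 | 0.91 |
| 4 | 0.333 | 0.58 | 0.85 |

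A simulation with 600 children, two log-scale recalls each, a REML fit and 20 replicates per r gave SD ratios of 0.81, 0.69 and 0.55.

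**Step 2: prevalence from shrinkage alone.** True prevalence is Φ(d); the tabulated predictions give Φ(d/√λ).

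| EAR position | True | r = 1 | r = 2 | r = 4 |
|---|---|---|---|---|
| d = −1, k = 2 | 15.9% | 11.0% | 7.9% | 4.2% |
| d = +0.5, k = 2 | 69.1% | 73.0% | 76.0% | 80.7% |
| d = +0.5, k = 10 | 69.1% | 70.0% | 70.8% | 72.3% |

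Example: d = −1, r = 2 gives Φ(−1/0.707) = Φ(−1.414) = 7.9%. The estimate is too low below 50%, too high above it, and unbiased at 50%.

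**Step 3: add a plain log back-transformation.** A child's mean intake is exp(μ + b + σ_w²/2), but plain back-transformation returns exp(μ + b). The understatement factor exp(σ_w²/2) is 1.08 at within-child log SD 0.4 (r = 1) and 1.38 at 0.8 (r = 4). With the EAR placed d SDs from the centre of log mean intake, the tabulated share is Φ((dσ_b + σ_w²/2)/(σ_b√λ)).

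For d = −1, k = 2, true 15.9%:
- r = 1: (−0.4 + 0.08)/(0.4 × 0.816) = −0.98, giving 16.4%.
- r = 2: (−0.4 + 0.16)/(0.4 × 0.707) = −0.85, giving 19.8%.
- r = 4: (−0.4 + 0.32)/(0.4 × 0.577) = −0.35, giving 36.5%.

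The low bias in step 2 has become nearly zero or reversed. The simulation with both errors agrees in pattern: a true 20% was estimated as 22%, 26% and 47%, and a true 50% as 61%, 72% and 92%.

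**Step 4: rescaling.** Multiplying predicted child deviations by 1/√λ restores the SD to σ_b, so the share below the cut-point on the transformed scale is Φ(d) for any r. Rescaling does not repair step 3, which needs the within-child variance brought into the back-transformation.

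**The case against.** The strongest reply is that the article describes the method briefly and cites a source that is not at hand. That source may rescale or simulate, and such details usually sit in a full analysis plan. This limits confidence. It does not dispose of the point, because the article does more than stay silent: it defines usual intake as the back-transformed predictions and proceeds to the cut-point. If the cited method does more, the definition misdescribes it.

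Other points that stand:
- The transformation, model terms and variance ratio are not stated. The λ formula is for an intercept-only model; between-child variance explained by covariates such as age is not shrunk.
- Two recalls are planned per round, but joint modelling of five rounds is not excluded. That makes shrinkage much milder, though not absent. It does nothing for the back-transformation error.

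Three stronger readings are tempting, and the document does not support them:
- A reader might infer that inadequacy is simply understated when the EAR lies below mean intake. That follows from shrinkage alone; step 3 shows it can reverse.
- A reader might infer that the EAR lies above mean intake for the micronutrients the ration supplies. The article gives neither intakes nor EAR values.
- A reader might infer that a planned between-arm test of inadequacy is distorted. Section 2.4.11 specifies no such test; its stated arm comparisons are anthropometric.

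**Conclusion.** The point holds as a bias in the procedure as written, without a fixed sign. Child-level predictions are too narrow for any r above zero: 82%, 71% or 58% of the true SD with two recalls, and 95%, 91% or 85% with ten, for assumed r of 1, 2 and 4. Shrinkage pushes prevalence away from 50%. An uncorrected log-type back-transformation pushes it upward. The net error depends on the nutrient, the transformation and the variance ratio, none of which the article gives, so the percentages above are illustrations and not forecasts for this trial.

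The reach is limited to the nutrient-inadequacy estimates within a secondary outcome. The primary WAZ analysis does not use them. Dietary diversity, minimum meal frequency and minimum acceptable diet are assessed from raw recall data under section 2.4.11 and are unaffected. This should be corrected, but it does not threaten the trial's main conclusion.

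**What to change.** Keep both recalls and the mixed model, and change what is taken from it:

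- Estimate the usual-intake distribution from the variance components, either by simulating child effects from the estimated between-child variance or by rescaling predicted child effects to that variance.
- Back-transform by integrating over the within-child variance, so that the target is a child's mean intake.
- Apply the EAR cut-point, and the probability method for iron, to that distribution.
- If inadequacy is reported by arm, fit the model by arm or include arm and visit, so that predictions are not drawn to a common mean.
- State whether rounds are modelled separately or jointly.

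If the cited method already includes these steps, correcting the definition in section 2.4.11 is enough. The cost is revised wording and some extra programming. No new data are needed.

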#### Study outcomes

2.4.5

The data for the longitudinal (individual-level outcome) and cross-sectional (population-level outcome) study components will be collected simultaneously at baseline (pre-intervention), and then at six-monthly intervals; i.e. at 6, 12, 18 and 24 months (endline). For the longitudinal or cohort component outcomes, the data collected at baseline, months 6, 12 and 18 months of intervention will be used to assess the key outcome and the trend in the cohort. Although the intervention will be implemented over 18 months, follow-up will continue until the endline at 24 months post-baseline. This extended follow-up period is aligned with the independent expert committee’s recommendations and allows for a more comprehensive assessment of the intervention’s effect, as key improvements in growth and nutritional outcomes are more likely to manifest over time.

For the cross-sectional component outcomes, the data collected between the baseline (month 0) and endline (month 24) will be used to assess the outcome and the trend (data at months 6, 12, and 18).

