##### Primary outcome

2.4.5.1

Change in weight-for-age z-score (WAZ), based on WHO growth standards, among children aged 6–36 months enrolled in the longitudinal component of the study, measured between baseline and 18 months of follow-up.

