#### Sample size

2.4.6

The sample size is calculated to detect a minimum mean difference of 0.3 in mean WAZ score between intervention and comparator arms, assuming a mean WAZ of −1.8 in the comparator group and a standard deviation of 1.0 in both groups (45, 46). With 80% power, 5% significance level, an intra-cluster correlation coefficient of 0.05, and an expected attrition rate of 20%, the estimated sample size is 300 per arm per site. This will be achieved through 30 clusters per arm, with an average of 10 children per cluster.

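### As written, the primary mixed model gives the tested time-by-arm term no clustering penalty, so its standard error will be too small if cluster trajectories vary

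*Protocol article*

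**What the plan says.** All references are to the protocol article.

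- Section 2.4.5.1 defines the primary outcome in the cohort: "Change in weight-for-age z-score (WAZ), based on WHO growth standards", "measured between baseline and 18 months of follow-up".
- Section 2.4.5 makes baseline one of the repeated measurements: "the data collected at baseline, months 6, 12 and 18 months of intervention will be used to assess the key outcome and the trend".
- Section 2.4.11 gives the model: "A linear mixed effects model with subject and cluster as random effects and an interaction term for time and intervention group will be performed". WAZ, LAZ and WHZ are analysed separately, within each site and pooled.
- In the same paragraph, the log-binomial comparison of stunting, wasting and underweight prevalence has "robust estimates of standard error accounting for clustering". No such provision is attached to the mixed model.
- On covariates, section 2.4.11 says: "Potential confounders (household food security, education, socioeconomic status, etc.) will be considered in the model". Baseline WAZ is not named, but the list is open-ended.
- Section 2.4.6 plans with "an intra-cluster correlation coefficient of 0.05", 30 clusters per arm per site and 10 children per cluster.
- Section 2.4.7 makes the health sub-centre the unit of randomisation.

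**The concern.** The treatment effect in this model is the time-by-arm interaction, which contrasts measurements within the same child and the same cluster. A child intercept and a cluster intercept add the same amount at every visit, so both drop out when baseline is subtracted from month 18. What remains in the model-based variance is residual variance divided by the number of children, with no between-cluster part.

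That is harmless only if clusters drift in parallel. There are reasons to expect otherwise. The package is delivered to all the children of a cluster by the same anganwadi staff, and rations reach each centre monthly (section 2.4.8.3). Recruitment may take two to four months (section 2.4.3.1), so visits in different clusters can fall in different seasons. If children of one cluster improve or falter together, the model counts that shared movement as independent noise in each child. Confidence intervals would then be too narrow and the false-positive rate above 5%. The same form is used for LAZ and WHZ.

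**Working it through.** **1. The plan's own sample size.** Inputs from section 2.4.6: difference 0.3, SD 1.0, 80% power, 5% significance (two-sided in section 2.4.11), ICC 0.05, 20% attrition, 30 clusters per arm, 10 children per cluster (8 after attrition).

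- Unclustered n per arm = 2 × ((1.96 + 0.8416)/0.3)² = 174.4.
- Design effect with 8 completers = 1 + 7 × 0.05 = 1.35; 174.4 × 1.35 = 235.5; 235.5/0.8 gives 295, which reproduces the stated 300.
- With 10 per cluster the design effect is 1 + 9 × 0.05 = 1.45, and the same steps give 317.

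So the design carries a clustering penalty of 1.35 to 1.45.

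**2. The penalty in the tested term.** Let K be clusters per arm, m children per cluster, σ²ct the cluster-by-time variance and σ²e the residual variance. For the arm difference in change from baseline to month 18:

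- variance under the random-intercept model = 4(σ²ct + σ²e)/(Km)
- true variance = 4(σ²ct + σ²e/m)/K
- ratio = 1 + (m − 1)ρ, with ρ = σ²ct/(σ²ct + σ²e)

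Neither the cluster nor the child intercept variance appears. K cancels from the ratio, so pooling six sites does not reduce the problem.

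**3. Assumed values (not in the documents).** Total variance is 1, of which 0.05 is between clusters. A share CAC (cluster autocorrelation) of that 0.05 is stable over time, so σ²ct = 0.05(1 − CAC). A share r of the remaining 0.95 is stable within the child, so σ²e = 0.95(1 − r). Here r runs from 0.6 to 0.8 and m from 8 to 10.

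Example with r = 0.7, CAC = 0.8, m = 8:

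- σ²ct = 0.05 × 0.2 = 0.010; σ²e = 0.95 × 0.3 = 0.285; ρ = 0.010/0.295 = 0.034
- variance ratio = 1 + 7 × 0.034 = 1.24
- model SE = √(4 × 0.295/240) = 0.0701; true SE = √(4 × (0.010 + 0.285/8)/30) = 0.0780; SE ratio 1.112
- type I error = 2 × (1 − Φ(1.96/1.112)) = 7.8%

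| CAC | Variance ratio | SE ratio | Type I error, closed form | Simulation (r = 0.7, m = 8) |
|---|---|---|---|---|
| 1.0 | 1.00 | 1.00 | 5% | 5.2% |
| 0.9 | 1.09–1.23 | 1.04–1.11 | 6.1–7.7% | 6.2% |
| 0.8 | 1.18–1.45 | 1.09–1.20 | 7.1–10.4% | 8.1% |
| 0.5 | 1.43–2.05 | 1.20–1.43 | 10.1–17.1% | 11.1% |

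The simulation used 4,000 null trials per scenario, 30 clusters per arm, four visits and categorical time. Its Monte Carlo error is about √(0.05 × 0.95/4000) = 0.3 percentage points near 5%.

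**4. Random slopes instead of cluster-by-visit noise (CAC 1.0, same simulation).** A cluster slope SD of 0.15 per 18 months gave 8.5%, a child slope SD of 0.4 gave 6.6%, and both together gave 10.2%. A cluster-level t-test on change stayed at 4.6–5.4% in every scenario of steps 3 and 4.

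**5. Baseline.** For two visits with equal variances and correlation r between them, the baseline-adjusted variance divided by the change-score variance is (1 − r²)/(2(1 − r)) = (1 + r)/2. This is 0.80 at r = 0.6 and 0.90 at r = 0.8.

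**The case against.** The strongest reply is that the article does not restrict the model to intercepts. Random slopes, residual covariance, coding of time and degrees of freedom are details that a condensed article may leave to a fuller plan. Cluster is in the model, and if trajectories do not vary the standard error is correct. This stands to the extent that the error is conditional and its size cannot be read from the documents. It does not dispose of the point: the section names the random effects for the primary analysis, the usual reading of that wording is intercepts, and the same paragraph adds clustering protection to another analysis but not to this one.

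A reader might infer more than the text supports in three ways.

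- **Moving the planning ICC onto change.** A ratio of 1.35 to 1.45 would give type I error of 9.2 to 10.4%. But the calculation in section 2.4.6 concerns a level: "The sample size is calculated to detect a minimum mean difference of 0.3 in mean WAZ score between intervention and comparator arms". With r = 0.7, a change ICC of 0.05 needs CAC = 0.7, since 0.05 × 0.3 = 0.015 and 0.015/(0.015 + 0.285) = 0.05. At CAC 0.9 the change ICC is only about 0.017.
- **Assuming linear time, or within-child correlation that decays and is modelled as constant.** The article states none of these. It lists discrete visits and fixes the contrast as baseline to 18 months.
- **Calling baseline WAZ unadjusted.** Baseline is in the outcome vector and the interaction compares change from it, which matches the stated outcome. A chance imbalance at baseline is differenced out. What is lost is precision; no bias arises.

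**Conclusion.** The point holds conditionally. On the ordinary random-intercept reading, a cluster-randomised trial whose sample size pays a clustering penalty of 1.35 to 1.45 would test its primary effect with a penalty of 1.00. Whether that inflates the false-positive rate depends on how far cluster trajectories diverge, for which the documents give no figure. Over the assumed range the nominal 5% test runs from no inflation, when clusters move in parallel, to about 17% at the extreme. A moderate departure (CAC 0.8 to 0.9) puts it at roughly 6 to 10%. It would be wrong to conclude that the standard error is certainly too small or that clustering is absent from the model. It is right to conclude that the stated model offers no protection if trajectories differ, and that nothing in the protocol justifies assuming they do not.

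**What to change.** In section 2.4.11, state for the primary model one of these:

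- a cluster-by-visit random effect in addition to the cluster and child effects;
- cluster-robust standard errors;
- a cluster-level analysis of change.

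The cluster-by-visit effect does not by itself cover child slopes that vary; the other two options do. Name the arm contrast at month 18 as the primary estimate, use small-sample degrees of freedom where a site with its 60 clusters is analysed alone, and apply the same form to LAZ and WHZ.

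As a separate gain in efficiency, which corrects no error, constrain the baseline mean to be equal in both arms or adjust for baseline WAZ. In a two-visit comparison this lowers variance by about 10 to 20% for an assumed baseline-to-18-month correlation of 0.8 to 0.6.

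The cost is analysis wording only, with no new data or participants, and it is best settled before unblinding. The downside is somewhat wider intervals from the clustering term. Within the assumed range this is affordable: the largest true standard error (0.0983, at r = 0.6, CAC 0.5, m = 8) still gives power Φ(0.3/0.0983 − 1.96) = 86% per site for a difference of 0.3.
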